# Virtual reality cognitive-behavioural therapy versus cognitive-behavioural therapy for paranoid delusions: a study protocol for a single-blind multi-Centre randomised controlled superiority trial

**DOI:** 10.1186/s12888-021-03473-y

**Published:** 2021-10-11

**Keywords:** Psychotic disorder, Paranoia, Delusions, Social anxiety, Virtual reality, Cognitive Behavioural therapy, Social functioning, Cost-effectivity

## Abstract

**Background:**

Seventy per cent of patients with psychotic disorders has paranoid delusions. Paranoid delusions are associated with significant distress, hospital admission and social isolation. Cognitive-behavioural therapy for psychosis (CBTp) is the primary psychological treatment, but the median effect size is only small to medium. Virtual reality (VR) has a great potential to improve the effectiveness of CBTp. In a previous study, we found that VR based CBT (VRcbt) for paranoid delusions is superior to waiting list. As a next step, a direct comparison with CBTp is needed. The present study aims to investigate whether VRcbt is more effective and cost-effective than regular CBTp in treating paranoid delusions and improving daily life social functioning of patients with psychotic disorders.

**Methods:**

A total of 106 patients with DSM-5 diagnosis of psychotic disorder and at least moderate level of paranoid ideations will be recruited for this multicentre randomized controlled trial (RCT). Patients will be randomized to either VRcbt or standard CBTp for paranoid delusions. VRcbt consists of maximum 16 sessions in virtual social situations that trigger paranoid ideations and distress, delivered in an 8–12 week time frame. Standard CBTp also consists of maximum 16 sessions including exposure and behavioural experiments, delivered in an 8–12 week time frame.

The two groups will be compared at baseline, post-treatment and six months follow-up. Primary outcome is the level of paranoid ideations in daily life social situations, measured with ecological momentary assessments (EMA) at semi-random moments ten times a day during seven days, before and after treatment. Every session, participants and therapists will rate the level of paranoid ideation and global clinical impression.

**Discussion:**

Comparison of VRcbt and CBTp will provide information about the relative (cost-) effectiveness of VRcbt for this population. VRcbt may become a preferred psychological treatment for paranoid delusions and social anxiety in patients with psychotic disorder.

**Trial registration:**

Netherlands Trial Register, NL7758. Registered on 23 May 2019.

**Supplementary Information:**

The online version contains supplementary material available at 10.1186/s12888-021-03473-y.

## Background

Seventy per cent of patients with schizophrenia and other psychotic disorders suffer from paranoid delusions, that are characterized by strong suspiciousness with the unfounded belief that other people are trying to harm them [1]. Paranoid delusions are associated with great distress, anxiety, depression, suicidal thoughts, and hospital admission [2, 3]. Furthermore, patients with paranoid delusions often experience problems in social functioning [4]. To avoid perceived threat, i.e., the fear that others may deliberately cause them harm, patients withdraw from social interactions and crowded places. This complicates daily life, as regular activities such as seeing friends, talking to people, shopping, walking on the street or using public transport pose a major challenge. Many patients are socially isolated, have small social networks, and are unemployed [5]. Since paranoid delusions and associated difficulties in social functioning cause a large burden on patients, effective interventions are of great importance. Main treatment options for schizophrenia and other psychotic disorders are antipsychotic medication and psychological treatment. A meta-analysis calculated a small to medium effect size of 0.44 for antipsychotic medication [6]. Many patients discontinue their medication regime due to the serious side effects of antipsychotics. Cognitive-behavioural therapy for psychosis (CBTp) is the main evidence-based psychological treatment for paranoid delusions [7]. CBTp for paranoid delusions aims to challenge delusional beliefs by means of cognitive restructuring and behavioural interventions such as exposure and experiments testing thoughts and beliefs. However, behavioural interventions are often too stressful for patients, as a result of which they avoid those interventions. Moreover, the meticulous preparation required preceding behavioural interventions is time-consuming for therapists, as a result of which this part of CBTp is often not properly performed in clinical practice [8]. Although CBTp is the most effective psychological treatment for paranoid delusions, a recent meta-analysis reported only a small to medium effect size of 0.36 [9]. Nearly half of the patients with schizophrenia and other psychotic disorders do not benefit from current treatments. Therefore, an improvement of treatment is urgently required. Virtual Reality (VR) has a great potential to improve psychological treatment of paranoid delusions. VR is the computer-generated simulation of a three-dimensional environment in which patients can interact with objects and virtual characters in a seemingly real or physical way using special electronic equipment, such as a helmet with a screen inside (head-mounted display, HMD). VR provides a powerful experience that can be used to help patients with paranoid delusions dealing with environments and social situations that make them paranoid or anxious [10]. In a controlled environment with a therapist’s guidance, patients can practice gradually with personalized exposure exercises and behavioural experiments in social situations. VR allows patients to repeatedly experience difficult daily life situations and practice new behaviour with direct feedback from the therapist. Also, patients are aware of the option to withdraw from the VR environments at any time, which makes VR exposure safer and more accessible compared to exposure within CBTp. The interactive nature of VR enables provocation of emotions and responses similar to real environments [11]. To summarize, VR provides an accessible, safe real-world experience in which patients can practice with difficulties in daily life while being coached by a therapist. Previous studies revealed emerging evidence of the potential to treat mental health problems with VR. In the treatment of patients with anxiety, VR has been proven effective and safe [11, 12]. VR is also safe to use in the treatment of patients with a psychotic disorder, and emerging evidence suggests its effectiveness [13]. A pilot study with thirty patients with psychosis reported a large effect size of 1.3 for a short VR based CBT (VRcbt) intervention targeting persecutory delusions, compared to virtual reality exposure [14]. Our group recently conducted the first randomized controlled trial (RCT) of VRcbt with 116 patients and showed that, compared to waiting list, VRcbt is effective for reducing paranoia (d = 1.6) and anxiety (d = 0.7) in patients with schizophrenia and related psychotic disorders [15]. Additionally, significant improvements were established for ideas of persecution, ideas of social reference, and use of safety behaviours. An advantage of VR, highly valued by both patients and therapists, was the possibility to start exposure immediately and successfully.

Moreover, VRcbt has the potential to improve mental health more cost-effectively. A recent meta-analysis of CBTp showed that patients with paranoid delusions are more likely to benefit from treatment when a higher number of CBTp sessions are offered [16], making CBTp time-consuming and expensive. Furthermore, the availability of CBTp is limited for patients with a psychotic disorder. Less than 10% of patients with psychosis are offered CBTp [17, 18]. Meanwhile, first evidence indicates that VRcbt has the potential to achieve positive results in fewer sessions compared to CBTp [14]. In our previous RCT, we aimed to get an impression of the short-term cost-effectiveness of VRcbt for patients with paranoid delusions compared to TAU, from a societal perspective. The VRcbt treatment condition was more expensive than TAU alone, which was to be expected, as VRcbt was added to regular treatment. The incremental cost-effectiveness ratio (ICER) per quality adjusted life year (QALY) gained, however, was within acceptable limits, as was the ICER for other relevant outcomes. At three month follow-up, the VRcbt group had lower health care costs and reduced costs due to productivity loss compared to the TAU alone group. Moreover, there were no psychiatric admission days for the VRcbt group at follow-up. To summarize, these results indicate acceptable cost-effectiveness of VRcbt, even in comparison to a waiting-list control condition without extra costs. In the current study, we take a next step by investigating effectiveness and cost-effectiveness of VRcbt by comparing VRcbt directly to CBTp.

### Objectives

In this RCT, we aim to investigate differences between VRcbt and CBTp in their effect on the level of paranoid delusion in daily life, level of social activities, proportion of time spent in social company, levels of distress, anxiety and depression. In addition, we aim to investigate the differences between groups in the mean number of sessions needed for clinically meaningful improvement of paranoid delusions in daily life. Finally, we aim to assess the differences between health care costs and production losses over the intervention and follow-up period. We hypothesize that VRcbt is more effective and cost-effective than CBTp for treating paranoid delusions and improving daily life social functioning of patients with schizophrenia and related psychotic disorders.

## Methods

This study is funded by the Brain Foundation Netherlands (grant number HA2017.01.04). The study has been approved by the medical ethical board of University Medical Centre Groningen, Groningen (NL66850.042.18), and is conducted in accordance with the Declaration of Helsinki. The study has been registered prospectively in the Netherlands Trial Register, trial number NL7758.

### Participants

Patients who receive treatment in ambulatory mental health care for a psychotic disorder are eligible for the study. Patients are recruited from Dutch and Belgian mental health treatment centres. We recruit participants in the following ways: 1) through advertisement of the study, by distributing posters and flyers at the participating centres, allowing participants to enrol themselves; and 2) through clinicians who inform their patients and refer eligible and interested participants to the study.

### Inclusion criteria

Patients must meet all of the following criteria to be eligible to participate:
DSM-5 diagnosis of schizophrenia spectrum or other psychotic disorder.At least a moderate level of paranoid delusions (Green Paranoid Thoughts Scale [19] > 40).Age 18–65 years.

### Exclusion criteria

Patients who meet any of the following criteria will be excluded from participation:
An estimated IQ below 70;Insufficient command of Dutch language.Received CBTp for paranoid delusions in the past 12 months.

### Design

This study is a single-blind multicentre randomized controlled trial (RCT) with two conditions: 1) VRcbt for paranoid delusions as experimental condition, and 2) CBTp for paranoid delusions as active control condition. Participants in both conditions may receive other types of treatment as usual, including antipsychotic medication, with the exception of CBT. The effects of the two conditions are compared at baseline (*T*_0_), at post-treatment (*T*_1_), and at three month follow-up (*T*_2_). A Consolidated Standards of Reporting Trials (CONSORT) inclusion flow diagram is shown in Fig. 1.

**Fig. 1 Fig1:**
[figure not shown]
CONSORT flow diagram

### Randomization and allocation concealment

Randomization will occur after completion of the baseline assessment. Block randomization will be used, with a block of eight random assignments for each participating mental health centre. The allocator will hide block size from the therapist and research assistants to prevent prediction of the next assignment. After a mental health centre has included eight patients, new blocks will be made available. Allocation to the two conditions will be in a 1:1 ratio. Randomization will be carried out by using the online randomization program www.randomizer.org by an independent researcher of the University Medical Center Groningen who is not involved in the trial. After the baseline assessment, the first author will enter the patients study ID into the online service and receive an email that details the patient’s allocation. The first author will then contact the therapist to inform them of the patients’ allocation. The therapist will then contact the patient about the allocation and to arrange the first therapy session.

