#### Procedure

Patients who might be eligible for participation will be contacted by their treating clinician and asked if they are interested in participating in the study. Clinicians will ask consent for sharing their contact information with the researchers after which interested patients will be informed about the study and screened by the researchers. After receiving written information about the study, patients will be given a consideration period of one week. If patients decide to participate after one week of consideration, written informed consent will be obtained first, and subsequently patients will complete the GPTS. If the GPTS score is > 40, patients are eligible for the study and the baseline assessment (T_0_) will continue. Following the baseline assessment, the baseline period of EMA will take place. After a week, patients are randomized to either VRcbt or CBTp. Patients allocated to either VRcbt or CBTp, will start with treatment. At the beginning of each session, participants complete the SDS and VAS. At the end of each session therapists complete the CGI. After the treatment period, a post-treatment (T_1_) takes place, followed by a seven days EMA. Finally, a follow-up (T_2_) assessment will be conducted six months after the start of treatment, followed by a final week of EMA. Patients who discontinue participation in the study at an early stage are requested to continue to participate in the measurements.

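### A single fixed block of eight per centre, with its size printed and not kept from the first author, conceals allocation less well than the protocol asserts

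*Protocol article*

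**What the plan says.** The section Randomization and allocation concealment fixes the scheme: "Block randomization will be used, with a block of eight random assignments for each participating mental health centre", and "Allocation to the two conditions will be in a 1:1 ratio". On the end of a block it says: "After a mental health centre has included eight patients, new blocks will be made available". The safeguard against guessing is that "The allocator will hide block size from the therapist and research assistants to prevent prediction of the next assignment".

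Randomisation is carried out "by an independent researcher of the University Medical Center Groningen who is not involved in the trial". Once baseline is complete, "the first author will enter the patients study ID into the online service", receives that patient's allocation by email and passes it to the therapist.

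Three other sections bear on the point:

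- Treatment quality and fidelity: the same therapists give both therapies and attend monthly group supervision at which current treatments are discussed.
- Participants: patients enter by clinician referral or by enrolling themselves after seeing a poster or flyer.
- Procedure: "interested patients will be informed about the study and screened by the researchers".

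**The concern.** The safeguard rests on keeping one number, the block size, from two groups of people. That is fragile for three reasons.

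1. The number is printed in the article, which still describes randomisation in the future tense. Any therapist or research assistant who reads it has the size.
2. The first author sees every allocation as it is made and is not named among those kept from the size. Coordinators, who under Assessment and blinding are told not to disclose allocation and so may know it, are not named either.
3. The simplest guess, that the next patient goes to the arm used less often so far, does not need the block size. Hiding the size cannot stop it.

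What is at stake is selection at entry. If someone who can guess the next arm influences who is referred or screened next, the groups may differ from the start. The primary outcome is self-reported momentary paranoia, and blinded assessors cannot undo a difference created before randomisation.

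**Working it through.** The protocol gives no predictability figure, so there is none to reproduce.

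**Inputs** (Randomization and allocation concealment): block size 8, fixed; stratified by centre; ratio 1:1. Assumption: 1:1 means 4 + 4 within each block. There are then C(8,4) = 70 equally likely blocks.

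**Step 1. Certain assignments, with the size and the centre's full history known.** An assignment is certain once one arm has used its four places. After k earlier assignments in the block this has probability 2·C(k,4)/70.

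| Position in block | k | Probability certain |
|---|---|---|
| 1st to 4th | 0–3 | 0 |
| 5th | 4 | 2/70 = 2.9% |
| 6th | 5 | 10/70 = 14.3% |
| 7th | 6 | 30/70 = 42.9% |
| 8th | 7 | 70/70 = 100% |

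The sum is 112/70 = 1.6 per block, or 1.6/8 = 20%. The closed form agrees: 2m/(m+1) with m = 4 gives 8/5 = 1.6. Over 106 patients this is 0.20 × 106 ≈ 21 assignments if every block fills. The number of centres is not given, and unfilled last blocks lower the count.

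**Step 2. Best guess.** Always guess the less-used arm and toss a coin at a tie. Expected correct guesses per block are m + 2^(2m−1)/C(2m,m) − 1/2 = 4 + 128/70 − 0.5 = 5.33, or 66.6%. Every completed block is balanced, so this needs only the centre's running imbalance. Knowing the size adds the ability to tell which guesses are certain.

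**Step 3. Guessing at referral instead of just before randomisation.** Under Procedure, a one-week consideration period and a one-week EMA period lie between first contact and randomisation, so the guess must be made at least two weeks ahead. The accrual rate is not stated, so the number of patients randomised at that centre in between is an assumption. Enumeration over the 70 blocks, with the block boundary known:

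| Other patients randomised in between | Certain | Best guess right |
|---|---|---|
| 0 | 20% | 67% |
| 1 | 7.5% | 60% |
| 2 | 2.1% | 58% |

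**Step 4. Randomly varying sizes.** Simulation of a guesser who sees the full centre history and knows the set of sizes but not their order (20,000 runs, 24 patients per centre):

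| Sizes | Certain | Best guess right |
|---|---|---|
| 8 fixed | 20% | 66.6% |
| 4, 6, 8 | 2.4% | 67.3% |
| 6, 8, 10 | 1.9% | 65.4% |
| 8, 10, 12 | 1.8% | 64.0% |

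Varying the size removes most of the certain predictions. It hardly changes the better-than-chance guess, and with 4, 6 and 8 it does not lower it at all.

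**The case against.** The strongest reply is that concealment of each individual assignment is in place. A researcher outside the trial carries out the randomisation, and each allocation is released singly, only after consent and baseline. Four fifths of assignments are never certain. Knowing the other fifth takes the block size, the block boundary and a complete centre history together, and a therapist who treats only some of a centre's patients sees only part of that history. The protocol does not say that therapists or screeners see a new block being released. Screening is by unnamed researchers, referral is by treating clinicians who are not stated to be trial therapists, and some patients enrol themselves. A better-than-chance guess exists in any unmasked trial that uses blocks, and a fixed eight is harder to guess than a fixed four (71%) or six (68%).

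Most of this stands and limits the size of the point. It does not restore the sentence in the protocol. The size is in print, the first author is left out of the restriction, and no passage separates people who learn allocations from people who refer or screen. Monthly supervision could also widen what a therapist knows, although the protocol does not say whether those groups follow centres.

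A reader might infer three stronger things: that the next assignment is generally predictable, that hiding the size gives no protection, or that the first author holds the list of future assignments. The documents support none of them. Most assignments are not determined. Hiding the size does withhold the certain predictions from people who truly do not know it. The first author is described as receiving one past allocation at a time.

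**Conclusion.** The point holds in a limited form: the allocation scheme is weaker than the protocol's sentence claims, but it is not broken. Up to 20% of assignments could be certain, and up to 67% guessed correctly, for a person who knows the block size and a centre's whole history at the moment of randomisation. Knowledge of the imbalance alone is enough for the 67%.

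Both figures are upper bounds. They assume 4 + 4 in each block, filled blocks, a complete history and no other patient randomised at that centre between the guess and the allocation. One or two patients in between bring the figures to 7.5% and 60%, or 2.1% and 58%. Whether anyone with that knowledge can influence entry is neither stated nor excluded, so bias is a possibility that the design leaves open and not something the documents show.

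**What to change.** 1. For blocks not yet released, have the independent researcher generate randomly varying block sizes within centre and disclose them in no document. Sizes 6, 8 and 10 are one example: certain assignments fall to about 2% and best-guess success to about 65%. Sizes 4, 6 and 8 would cut the certain assignments but not best-guess success.
2. Send each allocation directly from the independent researcher or the online service to the therapist, without passing through the first author.
3. State that nobody who sees allocations takes part in screening or eligibility decisions. This step matters most, because varying the size barely touches the simple guess.
4. Reword the sentence on hiding the block size so that it claims to reduce prediction and not to prevent it.

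If recruitment is too far advanced for a new list, make the change of wording and report who knew the block size and past allocations while referring or screening patients.

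The cost is a new list from the same independent researcher, one changed email route, and a slightly larger possible imbalance between arms from unfinished blocks.

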### Assessment and blinding

Assessments are carried out by independent research assistants blinded to treatment allocation. This is achieved by instructing coordinators, therapists and participants not to disclose group allocation to research assistants. Research assistants are instructed to stop the assessment in case of unblinding, and another research assistant will repeat the assessment. Other precautions include storing data revealing group allocation (e.g., therapist worksheets) in a separate location and using different assistants for each measurement as much as possible. Blinding is evaluated with a self-report form for research assistants at the end of the post-treatment and follow-up assessments. We will perform a sensitivity analysis by testing the treatment effect only for measurements where research assistants reported being completely blinded to group allocation.

